### Sample size

The sample size calculation is based on the primary outcome, the 6MWT. The power of the study is set on 80% (ß), using differences between two independent means with a 0.05 two-sided significance level. For calculation of the sample size, G*Power 3.1.9.2. was used [31]. Means and standard deviations (SDs) of the 6MWT of the study of Samuel et al. [19] were used. The first mean (SD) [483.16 (88.24)] is of patients with HNC who received the exercise intervention during (C/B)RT and the second mean (SD) [374.52 (110.26)] is of patients with HNC who received usual exercise care during (C/B)RT. Based on this, an effect size of 1.09 was calculated, which resulted in a sample size of 15 patients needed to undergo the PEI. We expect a drop-out of 24% as stated in the study of Samuel et al. [19]. Therefore, 20 patients need to be included in the PEI group. A feasibility study for PEI for patients with HNC in a Dutch population showed that 36% of the approached patients signed IC [13]. To include enough patients, a bigger sample size is needed. Using the expected participation percentage of 36%, a sample size of 56 is needed for the PEI group. Randomisation will be done in a 1:1 ratio so also 56 patients are needed in the control group. In total, 112 patients are needed. With the TwiCs design, two subgroups will arise in the PEI group, consisting of patients who accept and patients who refuse to undergo the PEI [26]. This type of non-compliance (refusal of the assigned treatment) will not be identical between the study arms [32]. Therefore, the sample size calculation will be revised when the real acceptance rate of the PEI differs from the initially estimated acceptance rate, before the end of the study [33].

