### Randomisation and blinding

At the first appointment the radiation oncologist will provide the study information. In Fig. 1, an overview is provided of the recruitment of patients. After enough time (until one week before the start of (C/B)RT) to consider their decision, the local investigator contacts the patient and asks to participate in the cohort. When the patient agrees, a baseline measurement (M0) will be planned. At the start of this measurement appointment, the patient will sign the IC for participating in the observational longitudinal cohort study. Immediately after the baseline measurement, the data collector will randomise the patient to participate in the experimental PEI or stay in the observational longitudinal cohort. Patients who refuse to participate will be listed and asked for their reason to refuse. When a randomised patient agrees to participate in the PEI, the first appointment for the PEI will be planned. During the first PEI appointment, the IC for PEI will be signed. For randomisation, a box with 112 sealed envelopes will be used. Fifty-six envelops contain ‘invite to undergo the experimental exercise intervention’ and 56 envelopes contain ‘no invitation to undergo the experimental exercise intervention’. This study will continue until 56 patients accepted the experimental PEI. The local investigator (YK) will perform the group allocation and data collection, so this researcher will not be blinded. The physiotherapists who will provide the intervention and the patients who undergo the experimental PEI will also not be blinded.

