### Primary outcome

Physical performance will be measured by the 6MWT [36]. The 6MWT measures the walking distance in meters of a patient in 6 min on a 10 m parkour.

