## Discussion

HNC itself, but also side effects of (C/B)RT sush as inadequate nutrition, weight loss, loss of muscle mass, loss of muscle strength, fatigue, and QoL can be deteriorated by a PEI [4]. Therefore, the aim of this study is to investigate and compare physical performance, muscle strength, fatigue, QoL, BMI, nutritional status, physical activity, treatment tolerability of (C/B)RT, and healthcare related costs in patients with HNC with and without a 10 week PEI during (C/B)RT. It has been demonstrated that PEI in patients with HNC during (C/B)RT is feasible and safe, reducing the deterioration of physical performance and QoL during (C/B)RT [9–20].

This study presents various practical and operational challenges which can involve the performance of this study. Blinding of the local investigator responsible for follow-up data collection is not feasible due to the small scale of the hospital, making it apparent which patient receives the PEI and which patient does not. Consequently, the local investigator performs both randomisation and data collection, a decision aimed at enhancing participant comfort and convenience by limiting interactions to one investigator.

With the intention to prevent a potential sample bias, a diverse and inclusive cohort of patients with HNC will be selected [48]. Consequently, the population participating in this study will be subjected to a varied spectrum of treatments within (C/B)RT. This comprehensive selection is made in the pursuit of enhancing the generalizability of the findings.

In clinical practice, patients receiving (C/B)RT experience a demanding and time-consuming schedule. Their schedule includes multiple appointments with healthcare professionals, including a radiation oncologist, dietician, and dental hygienist. This high frequency of appointments may lead to refusal of study participation [12]. In an effort to accommodate and facilitate participation, we prepared a strategy to schedule study appointments just before or after a patient’s usual care appointment at Instituut Verbeeten.

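### As described, the unblinded investigator who enrols patients and measures the 6MWT also draws each allocation, from a fixed 112-envelope box that does not fit the plan's own recruitment rules

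*Protocol article*

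**What the plan says.** All references are to the protocol article.

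- **Who enrols.** Under Randomisation and blinding, "the local investigator contacts the patient and asks to participate in the cohort".
- **Who allocates, and when.** In the same section, "Immediately after the baseline measurement, the data collector will randomise the patient". Cohort consent is signed at the start of that visit, so consent and M0 both come before the draw.
- **How.** "For randomisation, a box with 112 sealed envelopes will be used". Of these, 56 contain an invitation and 56 do not.
- **Who measures.** The local investigator "will perform the group allocation and data collection, so this researcher will not be blinded". The Discussion confirms that "the local investigator performs both randomisation and data collection". It gives two reasons: in a small hospital it is apparent who receives the programme, and a single contact person is more comfortable and convenient for patients.
- **What is measured.** The primary outcome is the 6MWT: "The 6MWT measures the walking distance in meters of a patient in 6 min".
- **How many.** Under Sample size, "Randomisation will be done in a 1:1 ratio so also 56 patients are needed in the control group", which gives 112 in total. The Abstract and the Participants section call this a minimum. Sample size also foresees a revision if actual acceptance departs from the estimate. Randomisation and blinding says that recruitment goes on until 56 patients have accepted the programme. Statistical analyses sets an interim look once 26 patients have undergone it.

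**The concern.** One person approaches the patient, measures the baseline walk, draws the envelope, and later measures the walk again knowing the arm. Walking distance depends on effort and encouragement, so unblinded assessment is already a known weakness, and the article discloses it. Secure allocation does not cure that weakness. It guards against a different one, selection, and here that guard lies with the same person.

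If an envelope were picked, or drawn again, after the patient's fitness or willingness had been seen, the invited and uninvited groups would no longer be comparable. Three things in the plan depend on that comparability or would be distorted with it:

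- the intention-to-treat comparison;
- the instrumental variable analysis, where random invitation is the natural instrument;
- the observed acceptance rate, which is to drive the sample-size revision.

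Separately, a box with 56 invitations has to serve a trial that is to continue until 56 patients accept.

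**Working it through.** **1. The plan's figure of 112.** Inputs from Sample size: means 483.16 and 374.52 m, SDs 88.24 and 110.26 m, 80% power, two-sided 0.05, drop-out 24%, acceptance 36%.

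- Effect size = (483.16 − 374.52) / √[(88.24² + 110.26²)/2] = 108.64 / 99.86 = 1.09.
- A two-sample t-test at this effect size needs 14.2, so 15 per arm.
- 15 / (1 − 0.24) = 19.7, so 20.
- 20 / 0.36 = 55.6, so 56 invited.
- 56 × 2 = 112.

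Every step reproduces. In this derivation 56 is the number *invited* and about 20 the number expected to accept.

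**2. Does the box fit the stopping rule?** In Randomisation and blinding, 56 is the number who *accept*.

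- Expected acceptors from 56 invitations at 36%: 56 × 0.36 = 20.2.
- Chance of reaching the interim trigger: P(at least 26 of 56 accept at 36%) = 0.07 (binomial).
- Chance that all 56 accept: 0.36^56 ≈ 1.4 × 10⁻²⁵.
- Invitations needed to expect 56 acceptors: 56 / 0.36 = 155.6, so 156, or 312 envelopes at 1:1.

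Other acceptance rates (assumed range, not from the article):

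| Acceptance | Invitations for 56 acceptors | Envelopes at 1:1 |
|---|---|---|
| 36% (plan) | 156 | 312 |
| 50% | 112 | 224 |
| 70% | 80 | 160 |
| 90% | 63 | 126 |
| 100% | 56 | 112 |

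The box is large enough only if everyone invited accepts.

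**3. How predictable is the box?** Suppose someone tracks the draws and always guesses the arm with more envelopes left.

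- Expected correct guesses = 56 + [4^56 / C(112,56) − 1] / 2 = 56 + (13.29 − 1)/2 = 62.1 of 112, or 55.5%.
- Expected number of final allocations known in advance = 2 × 56 / 57 = 1.96.
- A simulation of 20,000 boxes gave 55.5% and 1.95.

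Against 50% by chance, this is a small gain.

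**4. Do the stated reasons cover allocation?** That the arm is apparent in a small hospital explains why follow-up cannot be blinded. The convenience of one contact person explains why that person sees the patient. Neither requires that person to hold and draw the allocation, because a sequence prepared and released by someone else adds no patient contact.

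**5. What a disturbed draw would do.** Suppose the invited group were fitter by *b* metres through selection. The intention-to-treat difference would be biased by *b*. The article does not name its instrumental variable estimator. If it is the usual ratio estimator and no control patient receives the programme, the bias there is *b* / 0.36 = 2.8*b* at the planned acceptance. The article gives no basis for a value of *b*.

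**The case against.** The strongest reply is that this is a condensed article. It does not say who fills the envelopes, whether they are numbered or opaque, or whether openings are logged, and such details may stand in the full protocol. A reader might infer that the draw leaves no trail and cannot be audited. The article does not support that, because it is silent on the matter. What stands without inference is the concentration of roles, which the article states and then defends.

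The text also contains real safeguards. The envelopes are sealed, all cohort patients are randomised, and the draw follows consent and baseline, so a patient's own allocation cannot influence their M0 value or their decision to join. This limits selection at entry. It does not prevent a choice or a second draw at the moment of allocation, when fitness is known.

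Predictability is small, and a guess could act only on whom to approach. That is correct, and predictability is not the main point.

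A reader might also infer that allocation cannot go past 112. Nothing forbids adding envelopes. The accurate statement is that no rule for doing so is given, although three of the plan's own rules may require it.

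Finally, unstratified 1:1 allocation is valid, and the Discussion accepts a mixed treatment population on purpose. Not stratifying by RT versus CRT/BRT is no error.

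**Conclusion.** The point holds for the procedure as described. One unblinded person enrols, allocates and measures the primary outcome. No independent preparation or release of the allocation is described, and the reasons given do not call for that person to control it. This leaves an avoidable opening for selection after baseline. A reader might infer that allocations will be subverted. The article gives no evidence of that, and the resulting bias cannot be quantified from it.

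The mismatch between box and recruitment rules can be quantified. Assuming 36% acceptance and independent decisions, 56 invitations yield about 20 acceptors, with a 7% chance of reaching the 26 needed for the interim look and practically none of reaching 56. The derivation of 112 is not disturbed by this. What needs reconciling is whether 56 means invited or accepting patients, and how allocation proceeds after the last envelope.

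The change should be made: it is a cheap improvement to the design, and not a flaw that invalidates it.

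**What to change.** - Replace the box with a computer-generated 1:1 list with random, undisclosed block sizes, prepared by someone without patient contact. Avoid very short blocks: by the formula above, a known block of four gives 2 + (16/6 − 1)/2 = 2.83 correct guesses of 4 (71%), worse than the box.
- Release allocations one at a time, with a dated log, only after consent and M0 values are saved. Sequentially numbered opaque envelopes, prepared and logged independently, are an acceptable alternative.
- Make the list extendable beyond 112, and state how allocation continues after a sample-size revision.
- Reconcile the rule of recruiting until 56 accept with the Sample size section, where 56 are invited, and with the interim trigger of 26.
- If numbering, independent preparation or a log already exist in the full protocol, say so. The remaining change is then to take the draw out of the assessor's hands and settle the numbers.

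The cost of the allocation change is a few hours of set-up and a short protocol edit, with no extra assessor. Settling the recruitment target may change the planned number of patients, and that is a separate decision. Stratifying by RT versus CRT/BRT is optional.

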**Methods:**

This study, based on a trial within cohorts (TwiCs) design, will contain a prospective cohort of at least 112 patients. Fifty-six patients will randomly be invited for an experimental 10 week PEI. This PEI consists of both resistance and endurance exercises to optimize physical performance, muscle strength, fatigue, QoL, BMI, nutritional status, physical activity, and treatment tolerability of (C/B)RT. Measurements are at baseline, after 12 weeks, 6 months, and at 12 months. Statistical analyses will be performed for intention-to-treat and instrumental variable analysis.

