### Participants

At least 112 patients will be recruited at Instituut Verbeeten, Tilburg, the Netherlands. This hospital is specialized in treating patients with HNC of which approximately 100 patients are treated with (C/B)RT yearly. Patients with HNC scheduled for (C/B)RT will be recruited by the radiation oncologist. First, patients will receive a letter explaining the study aims and procedures. Second, patients who have expressed their interest will be contacted by the local investigator and procedures will be explained in more detail. When a patient agrees, a baseline visit will be scheduled to obtain written IC and perform baseline evaluation measurements.

Patients treated with RT receive 30 times 2,2/2,1gray (Gy). Patients treated with CRT or BRT will receive seven times Cisplatin or Nivolumab combined with 35 times 2 Gy RT. This treatment will be adapted when necessary. All patients with HNC receive advices based on the ‘Dutch physical activity guideline’ [28]. Just before and during (C/B)RT, nutritional care is provided by a dietician on a weekly basis, focusing on optimal energy balance and prevention of negative energy balance.

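### The number 56 means patients invited in the sample size section but patients who accept in the randomisation section, so the end of recruitment is not defined

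*Protocol article*

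**What the plan says.** The Sample size section of the protocol article works in steps. Fifteen patients must undergo the intervention, 20 after allowance for 24% drop-out, and 56 after allowance for 36% participation. With 1:1 randomisation there are 56 controls, and "In total, 112 patients are needed". The section states that the intervention arm will contain both acceptors and refusers, so this 56 counts patients invited. The abstract agrees: "Fifty-six patients will randomly be invited for an experimental 10 week PEI". The abstract and the Participants section both give 112 as a minimum.

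Randomisation and blinding starts in line with this: "For randomisation, a box with 112 sealed envelopes will be used", half of them invitations. It also expects refusals, since refusers are to be listed with their reasons. It then states: "This study will continue until 56 patients accepted the experimental PEI".

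Two further places bear on the point. Sample size says the calculation will be revised if the observed acceptance rate differs from the estimate. Statistical analyses places an interim analysis, meant to check the power calculation, after 26 patients have undergone the intervention.

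**The concern.** The same number carries two meanings. Under one, 56 is the size of the invited arm and about 20 of those patients take up the intervention. Under the other, 56 is the number who take it up, and the invited arm must be larger by the reciprocal of the acceptance rate, or about 2.8 times at 36%.

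This sentence decides when the trial ends, and so its size, duration and power. Followed literally, the envelopes run out at patient 112 with the end condition unmet, and the article does not say how later patients are allocated. That matters more than usual here because the local investigator both allocates patients and collects the data, unblinded.

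**Working it through.** **Inputs** (Sample size section unless stated)
- Two-sided 5% level, 80% power, comparison of two independent means.
- Six-minute walk distance: 483.16 m (SD 88.24) with exercise, 374.52 m (SD 110.26) with usual care.
- Drop-out 24%; participation 36%; 1:1 allocation.
- 112 envelopes, 56 of them invitations (Randomisation and blinding).
- Interim after 26 treated patients (Statistical analyses).
- About 100 patients treated per year (Participants).

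**1. The plan's own figure reproduces.**
- Difference: 483.16 − 374.52 = 108.64 m.
- Pooled SD: √[(88.24² + 110.26²)/2] = 99.86 m.
- Effect size: 108.64/99.86 = 1.088, stated as 1.09.
- Two-sample t-test (noncentral t): power 0.79 with 14 per group and 0.82 with 15, so 15 per group.
- Drop-out: 15/0.76 = 19.7, so 20.
- Participation: 20/0.36 = 55.6, so 56 invited; 1:1 gives 112.

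The 56 in this chain is therefore a number invited.

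**2. Expected acceptors from the box.** 56 × 0.36 = 20.2.

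**3. Size under the acceptance rule.** With acceptance rate a, 56 acceptors need 56/a invited and 112/a randomised at 1:1.

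| Acceptance a | Invited, 56/a | Randomised, 112/a |
|---|---|---|
| 36% (protocol's assumption) | 155.6 | 311 |
| 50% | 112 | 224 |
| 70% | 80 | 160 |
| 80% | 70 | 140 |
| 100% | 56 | 112 |

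Rounding up by arm at 36% gives 312. The two rules agree only at 100% acceptance. At about 100 treated patients a year, 311 patients would take 311/100 = 3.1 years even if every treated patient were eligible and joined.

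**4. Interim trigger.** With 56 invited and 36% accepting, the binomial probability of at least 26 acceptors is 0.07. To expect 26 acceptors, 26/0.36 = 72 patients would have to be invited, more than the box allows.

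**5. Intention-to-treat power under each rule.** Assumptions: refusers in the invited arm respond like controls, and 24% drop out in both arms.
- Diluted difference: 0.36 × 108.64 = 39.1 m.
- With the SD unchanged: d = 0.36 × 1.088 = 0.392.
- With the invited arm as a mixture of acceptors and refusers: variance = 0.36 × 88.24² + 0.64 × 110.26² + 0.36 × 0.64 × 108.64² = 2803 + 7781 + 2719 = 13303. Averaged with the control variance of 12157, the SD is 112.8 m and d = 39.1/112.8 = 0.347.
- 112 randomised: 56 × 0.76 = about 43 per arm; power 0.43 (d = 0.392) or 0.35 (d = 0.347).
- 311 randomised: 155.6 × 0.76 = about 118 per arm; power 0.85 or 0.76.

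**The case against.** The best defence is that the article foresees a larger trial. It gives 112 as a minimum, promises a revised sample size if acceptance differs from the estimate, and plans an interim look at power. Recruiting beyond 112 is thus not in itself a contradiction. That stands, but it does not remove the conflict. The revision applies when acceptance departs from the estimate, whereas the two rules already disagree at exactly 36%. A minimum of 112 also supplies neither a second target nor further envelopes.

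The sentence may be a slip, with accepted written for invited. That is plausible, but the interim trigger makes it unsafe to assume: 26 treated patients is close to half of 56 and fits the acceptor reading better.

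A reader might infer three stronger things that the document does not support:
- **That the trial really is one of 311 patients.** This figure holds only at 36%. The article takes that rate from a feasibility study, as the share of approached patients who consented, and applies it to patients who have already joined a cohort. Their acceptance could well differ, hence the range above.
- **That staff may stop whenever it suits them.** Nothing in the text says so. What it supports is that the end point is ambiguous.
- **That no allocation sequence exists beyond patient 112.** A condensed article may leave out how envelopes are replenished. It is fair to say only that none is described.

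The power figures rest on assumptions of their own, and the contradiction does not depend on them.

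**Conclusion.** The text is wrong as written. The abstract and the Sample size section count 56 as invited; the end-of-study sentence counts 56 as accepted; and the box makes the second impossible as soon as one invited patient refuses. This holds at any acceptance rate below 100%.

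The size of the gap does depend on that rate: 112 against about 311 randomised at the protocol's 36%, narrowing to 112 against 140 at 80%. The interim trigger adds to the inconsistency, since it would probably not be reached under the 112 plan. Under the dilution and drop-out assumptions stated, the choice of rule separates a trial well below 80% intention-to-treat power from one near it. It needs correcting because the trial's size cannot be determined from the document.

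**What to change.** Define the end of recruitment once, in patients randomised.

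- **Preferred.** Replace the end-of-study sentence in Randomisation and blinding with: recruitment continues until 112 patients (56 invited, 56 not invited) have been randomised, or the revised number after the planned sample size review. In Statistical analyses, set the interim trigger to a number that can be reached under that target, preferably in patients randomised. Say how the allocation sequence is extended if the review raises the number.
- **If 56 acceptors is truly intended.** Align the abstract, Participants, Sample size and Randomisation and blinding with the resulting total (about 311 at 36%), and prepare an allocation list of that length.

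In either case, state the intention-to-treat power for the chosen number with its assumptions.

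Cost: if 112 is kept, wording changes in two sections and an openly less favourable power statement (about 35-43%). If 56 acceptors is kept, a larger trial, lasting more than three years at 36% acceptance even if every treated patient joins.
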